#### Exclusion criteria

2.3.2

Participants will be excluded for any of the following:
Congenital structural brain malformations.Seizures attributable to a metabolic cause (e.g., electrolyte imbalances or hypoglycemia).Transfer to a non-participating center or voluntary discharge prior to enrollment.Refusal of informed consent by the parent or guardian.

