Prognostication of motor outcome following neonatal stroke has been an active area of research. Magnetic resonance imaging (MRI) assessment of the posterior limb of the internal capsule (PLIC) has been shown to correlate with the development of hemiparesis (11, 12). Quantitative scoring systems such as the Modified Pediatric ASPECTS have also been developed to correlate infarct volume with clinical outcomes (13). Additionally, the Hammersmith Infant Neurological Examination (HINE) and general movements evaluation are validated tools for early prediction of cerebral palsy (12). We acknowledge that this registry enrols only diagnosed cases; therefore, cumulative incidence will be calculated using total live births from all 22 participating hospitals as the denominator. However, this represents a hospital-based cohort rather than true population-based surveillance, and referral patterns may bias incidence estimates.

Shenzhen is particularly suitable as a model region due to its annual birth rate of approximately 200,000 live births, >98% NICU coverage across all districts, universal availability of cranial MRI and video-EEG at all participating hospitals, and the fact that >95% of regional births occur within the 22 study hospitals.

Therefore, establishing a prospective, multicenter cohort and dedicated registry is an urgent and foundational step. Such a resource is essential for accurately defining the disease burden, identifying associations with prenatal and perinatal factors that may inform future interventional studies, and mapping the evolution of neurodevelopmental outcomes from infancy through early childhood. By capturing comprehensive, longitudinal data within a real-world clinical setting, a registry can bridge the critical evidence gap between isolated clinical observations and population-level understanding.

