#### Inclusion criteria

2.3.1

Participants must meet all the following criteria:
Gestational age ≥28 weeks and ≤28 days postnatal, with identified stroke risk factors. (Extremely preterm infants <28 weeks are excluded by design due to diagnostic challenges and different pathophysiology.Clinical presentation of acute encephalopathy or seizures.Neuroimaging confirmation (MRI) of stroke (arterial ischemic, hemorrhagic, or cerebral venous sinus thrombosis), excluding other common etiologies. Clinically silent infarctions (incidental findings on imaging without clinical symptoms) will be excluded. To ensure complete case ascertainment, all neonates with identified risk factors for stroke (e.g., congenital heart disease, extracorporeal membrane oxygenation, or severe perinatal asphyxia) will undergo systematic screening with cranial MRI, and any asymptomatic infarctions detected will be documented separately but excluded from the primary analysis cohort**.**Parental or legal guardian consent.

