#### Recruitment, screening, and informed consent

2.4.1

Neonates meeting the inclusion criteria will be prospectively identified and recruited by trained neonatologists from the NICUs and pediatric wards of the 22 participating hospitals. Two attending neonatologists at each site will be responsible for patient enrollment using standardized diagnostic criteria.

Written informed consent will be obtained from the parents or legal guardians after a definitive diagnosis is made. The study adheres to the ethical principles of the Declaration of Helsinki and has received institutional ethics approval.

To ensure rigorous standardization across the 22 participating centres, all enrolling neonatologists will undergo a mandatory centralized training workshop focused on standardized case definitions, MRI interpretation using a validated study atlas, and EEG acquisition protocols. In parallel, to maintain longitudinal data quality, annual inter-rater reliability assessments will be conducted using 10 blinded test cases. For diagnostic adjudication, all stroke subtypes will be centrally reviewed by an expert committee comprising three senior neonatologists and two neuroradiologists at Shenzhen Children's Hospital, who remain blinded to the initial site-level diagnosis. Furthermore, neuroimaging will adhere to a harmonized 3T MRI protocol (including DWI, SWI, and MRA/MRV sequences). Where 3T MRI is not immediately available at a participating center, arrangements will be made for patient transfer to a center with 3T capacity, and this will be documented. Specific scoring approaches for infarct volume (modified Pediatric ASPECTS) and PLIC assessment will be used centrally. All video-EEG recordings will be centrally interpreted by a single epileptologist masked to all clinical and imaging data.

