#### Primary outcomes

2.5.1

Registry-based incidence of neonatal strokes in Shenzhen.

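### The primary incidence counts only enrolled cases but all live births, so for infants born in the 22 hospitals it is understated by the share of eligible diagnosed cases not enrolled

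*Protocol article*

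**What the plan says.** The only outcome listed under Primary outcomes (2.5.1) is "Registry-based incidence of neonatal strokes in Shenzhen". The Introduction gives the denominator: "cumulative incidence will be calculated using total live births from all 22 participating hospitals as the denominator". The same sentence describes the case source: "We acknowledge that this registry enrols only diagnosed cases".

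Entry is conditional. The inclusion criteria (2.3.1) require "Parental or legal guardian consent". The exclusion criteria (2.3.2) list "Refusal of informed consent by the parent or guardian" and "Transfer to a non-participating center or voluntary discharge prior to enrollment". Section 2.4.1 sets the order of events: "Written informed consent will be obtained from the parents or legal guardians after a definitive diagnosis is made".

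One group outside the cohort is to be recorded. Under 2.3.1, "any asymptomatic infarctions detected will be documented separately but excluded from the primary analysis cohort". The article describes no similar record for refusals, transfers or voluntary discharges. Its caveat on incidence, in the Introduction, names the hospital-based design and referral patterns.

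**The concern.** The numerator carries conditions that the denominator does not. Because consent follows a definitive diagnosis, an infant whose parents decline is already a confirmed case at that moment. Under the stated rules this infant does not enter the registry, yet the birth still counts among the live births, so in the incidence calculation it is a birth without stroke.

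A larger sample does not reduce this error, and later analysis cannot correct it if nobody recorded how many cases were lost. Section 2.7 plans incidence by gestational age, sex, birth weight and hospital level. If refusal or early departure differs across those strata, the comparisons between them are distorted too. A low rate in one stratum could not be told apart from low enrolment there.

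**Working it through.** **The plan's own figure.** The article states no expected incidence, precision or non-enrolled share for the primary outcome. Its only related figure, in section 2.6, is about 210 evaluable participants from 300 enrolled. It reproduces: 300 × (1 − 0.10 − 0.20) = 210 (applied in sequence, 300 × 0.90 × 0.80 = 216). Those 10% and 20% allowances are for death and loss to follow-up after enrolment. They say nothing about cases lost before it.

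**Inputs**
- Annual live births: about 200,000 (Introduction).
- Share born in the 22 hospitals: above 95% (Introduction); 0.95 is used.
- Period: six years, January 2025 to December 2030 (2.2).
- Incidence of strictly neonatal stroke: 1 in 3,000 to 1 in 5,000 (Introduction).
- Non-enrolled share f: not given; 10%, 20% and 30% are assumed.

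**Formula.** Let B be live births at the 22 hospitals, D the eligible diagnosed cases among them, f the share of D not enrolled, and O the enrolled cases born elsewhere.
- Reported incidence = [D(1 − f) + O] / B.
- Among in-network births only (O = 0), reported / true = 1 − f, so the relative bias is −f.

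**Numbers**
- B = 200,000 × 0.95 × 6 = 1,140,000.
- At 1 in 3,000, D = 1,140,000 / 3,000 = 380.

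| f | Cases counted | Reported rate | Exact 95% Poisson interval (cases) | Contains 380? |
|---|---|---|---|---|
| 10% | 342 | 1 in 3,333 | 307 to 380 | Only just |
| 20% | 304 | 1 in 3,750 | 271 to 340 | No |
| 30% | 266 | 1 in 4,286 | 235 to 300 | No |

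- At 1 in 5,000, D = 228. With f = 20%, about 182 are counted (1 in 6,250), interval 157 to 210, which excludes 228.
- From the recruitment target: 300 enrolled gives 1,140,000 / 300, or 1 in 3,800, with an exact interval of 267 to 336 cases. The true count 300 / (1 − f) passes 336 when f exceeds 1 − 300/336 = 10.7%.

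Both routes put the point at which the loss exceeds random error at roughly 10%.

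**Cases born elsewhere.** Recruitment is from NICUs and pediatric wards (2.4.1), and no criterion limits place of birth. The two errors cancel when O = f × D. With D = 380 and f = 20%, that would take 76 enrolled infants born outside the network. The article gives neither f nor O.

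**The case against.** The strongest reply is that no sentence says the incidence numerator is the consented, enrolled cases. Section 2.4.1 has infants identified before they are recruited, 2.3.1 states an aim of complete ascertainment, and a screening log is the kind of detail a condensed article leaves to the full protocol. This stands in part: the numerator is read from several places together. However, the outcome is named as registry-based, the registry is said to enrol its cases, the entry rules are stated, and no other case source is described. Followed as written, the rules and the denominator do not match.

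Other points stand and limit the finding.
- The referral caveat in the Introduction partly covers transfer to a non-participating center. It does not cover refusal, or voluntary discharge after diagnosis.
- Some infants leaving before enrolment may not yet be diagnosed. A count of MRI-diagnosed cases would miss them as well.
- The size is assumed. At 10% loss the interval still just includes the true count.

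A reader might go further in three ways, none of which the document supports. One is that the reported rate as a whole must be too low by f; enrolled infants born elsewhere act in the opposite direction. Another is that consent loss explains the gap between 1 in 2,660 and 1 in 8,373; the Introduction attributes that gap to type of case-finding, imaging and referral, and does not mention consent. The third is that cases may plainly be counted without consent; that is for the ethics committee.

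**Conclusion.** The mismatch is real and affects the only listed primary outcome. For infants born in the 22 hospitals, incidence is understated by exactly the share of eligible diagnosed cases not enrolled. The direction and the formula follow from the stated rules, provided the numerator is the enrolled cases, which is the direct reading. The size does not follow: it depends on an assumed f, and matters beyond sampling error only when f is above roughly 10%. The direction of the net bias in the published rate is open, because the number of enrolled infants born elsewhere is also unknown. Since no count of non-enrolled cases is described, the study as written could end without being able to state either quantity. That makes it worth settling while cases are being collected.

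**What to change.** Separate the incidence numerator from cohort enrolment.
- Subject to ethics approval, keep at each hospital a de-identified count of every eligible MRI-diagnosed case, whatever the consent, transfer or discharge status. Record birth hospital and the planned strata (gestational age, sex, birth weight, hospital level), plus subtype.
- State in 2.5.1 and 2.7 that the primary numerator is the counted cases born in the 22 hospitals, so that numerator and denominator cover the same births. Report cases born elsewhere separately.
- Keep consent as a condition for follow-up and biobank only, and report enrolled over diagnosed cases by hospital.
- If the count is not permitted, label the outcome as incidence of enrolled neonatal stroke, and report by hospital the numbers refused, transferred and discharged before enrolment.

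The cost is a change of wording, an ethics amendment and a short log at each site. No visit or assessment is added. The count will still miss infants who leave before diagnosis, and the report should say so.

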#### Withdrawal criteria

2.3.3

Participants will be withdrawn from the study if:
The participant or legal guardian withdraws consent.The participant fails to complete scheduled follow-up assessments.Clinical deterioration renders continued participation unsafe or impractical.

#### Elimination criteria

2.3.4

Participants will be eliminated from the final analysis if:
No data is recorded throughout the study.Serious protocol deviations occur (e.g., unapproved concomitant therapies and noncompliance with key procedures).Medications or interventions that could confound results are administered during the study.

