#### Secondary objectives

2.1.2

To characterize the clinical presentation, short-term treatment efficacy, and safety of the three subtypes of neonatal stroke: arterial ischemic stroke, cerebral sinovenous thrombosis, and hemorrhagic stroke.To identify significant prenatal, perinatal, and postnatal risk factors for neonatal stroke, and to develop and validate predictive models for risk stratification using a panel of early biochemical and imaging biomarkers.To analyze regional and institutional variations in the diagnostic, therapeutic, and rehabilitative management of neonatal stroke, and to propose evidence-based strategies for optimizing care and standardizing treatment protocols.

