### Study design

2.2

This multicenter, prospective, observational cohort study aims to investigate the long-term neurodevelopmental outcomes of neonates with stroke. The study is planned to run for six years, from January 2025 to December 2030, in Shenzhen, China. The initial network comprises 22 collaborating hospitals, with Shenzhen Children's Hospital as the lead institution and Shenzhen People's Hospital as the primary coordinating center.

The study aims to recruit 300 neonates diagnosed with neonatal stroke, following them prospectively for five years to assess their neurodevelopmental trajectory. Additional hospitals may be included throughout the study period. A detailed study flow diagram is presented in Figure 1.

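### Section 2.3.4 drops children from the final analysis for treatment received after enrolment, in an observational registry set up to study treatment; the withdrawal rules in 2.3.3 add prognosis-related loss

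*Protocol article*

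**What the plan says.** The Study design section (2.2) describes the project as follows: "This multicenter, prospective, observational cohort study aims to investigate the long-term neurodevelopmental outcomes of neonates with stroke". No therapy is allocated.

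The Elimination criteria (2.3.4) open with "Participants will be eliminated from the final analysis if". Two of the three criteria that follow are at issue:

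- "Serious protocol deviations occur (e.g., unapproved concomitant therapies and noncompliance with key procedures";
- "Medications or interventions that could confound results are administered during the study".

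The removal is not confined to any one outcome or analysis.

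The Withdrawal criteria (2.3.3) take a child out of the study on withdrawal of consent and in two further situations:

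- "The participant fails to complete scheduled follow-up assessments";
- "Clinical deterioration renders continued participation unsafe or impractical".

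The first secondary objective (2.1.2) is "To characterize the clinical presentation, short-term treatment efficacy, and safety of the three subtypes of neonatal stroke", and the third concerns regional and institutional differences in diagnosis, therapy and rehabilitation. Section 2.4.3 has a registry module for therapies and records epilepsy medication at follow-up. Section 2.5.2 lists survival over five years and a 5-year composite that includes epilepsy. The limitations in the Discussion note that antiepileptic strategies may change during the study, and promise to document major practice changes and adjust for them.

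**The concern.** The elimination rules read like per-protocol rules for a drug trial. In a registry, the treatment a child receives is an observation, and some of the objectives are about exactly that. Removing children because of it conditions the analysis set on an event after enrolment that is probably related to severity, hospital and outcome.

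Four results are exposed: the 5-year neurodevelopmental outcome (part of the primary objective in 2.1.1), survival, the comparison of management between hospitals, and the prognostic model, which would be developed on a different group from the one it is meant for. Because elimination is not limited to one outcome, it is also unclear whether an eliminated case still counts in the incidence numerator, which is the primary outcome.

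The withdrawal rules have a related effect. A child withdrawn for incomplete follow-up may lose a 5-year outcome that could still have been observed. Withdrawal for deterioration is tied to prognosis by its nature.

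**Working it through.** **1. The elimination rule against the rest of the protocol**

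| Place | What it requires | Under 2.3.4 |
|---|---|---|
| 2.2 | Observational design, no assigned therapy | There is no assigned regimen for a concomitant therapy to depart from |
| 2.1.2, first objective | Treatment efficacy and safety by subtype | Children with possibly confounding treatment are removed |
| 2.1.2, third objective | Variation in therapy and rehabilitation | Part of the variation is removed |
| 2.4.3 | Therapies and epilepsy medication recorded | The data are collected, then the child is dropped |
| 2.5.2 | Epilepsy is part of the 5-year composite | Read literally, medication for an outcome component could trigger removal |
| Discussion, limitations | Adjust for changes in practice | Adjustment needs the treated children in the data |

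**2. The plan's own figures (2.6)**

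Inputs: 300 enrolled, 10% mortality, 20% loss to follow-up, 30% outcome rate, 6 to 8 candidate predictors.

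- Evaluable: 300 × (1 − 0.10 − 0.20) = 210. Applied in sequence, 300 × 0.90 × 0.80 = 216. The stated figure of about 210 is reproduced.
- Events: 0.30 × 210 = 63, leaving 147 non-events.
- Events per variable: 63/6 = 10.5 and 63/8 = 7.9.

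The allowance covers death and loss to follow-up. It contains nothing for elimination under 2.3.4.

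**3. Illustration of elimination**

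Let a be the share of events removed and b the share of non-events removed. Both are assumptions; the document gives neither.

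Observed rate = 63(1 − a) / [63(1 − a) + 147(1 − b)]

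| a | b | Events | Children | Observed rate | Events per variable (8 or 6 predictors) |
|---|---|---|---|---|---|
| 0 | 0 | 63 | 210 | 30.0% | 7.9 or 10.5 |
| 10% | 10% | 56.7 | 189.0 | 30.0% | 7.1 or 9.5 |
| 20% | 10% | 50.4 | 182.7 | 27.6% | 6.3 or 8.4 |
| 30% | 10% | 44.1 | 176.4 | 25.0% | 5.5 or 7.4 |
| 50% | 10% | 31.5 | 163.8 | 19.2% | 3.9 or 5.3 |

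Equal removal costs precision but does not shift the rate. The shift in the last three rows comes from assuming that events are removed more often. If non-events were removed more often, the rate would rise.

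**4. Illustration of loss, including withdrawal under 2.3.3**

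These children fall within the 20% and 10% allowances, so the expected count of 210 does not change. The question is who is lost. There are 300 − 30 = 270 expected survivors, with 0.30 × 270 = 81 events, and 60 are lost. If the outcome rate among the lost is q (assumed), the observed rate is (81 − 60q)/210:

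- q = 40%: 57/210 = 27.1%
- q = 50%: 51/210 = 24.3%
- q = 60%: 45/210 = 21.4%

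**The case against.** Several points on the other side are sound.

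- **Withdrawal is not elimination.** Section 2.3.3 takes children out of the study; only 2.3.4 takes them out of the final analysis. A reader might infer that withdrawal erases data already collected, but nothing says so.
- **The triggers in 2.3.3 are qualified.** A reader might infer that one missed visit, or any worsening, is enough. The text speaks of assessments in the plural without saying how many, and limits deterioration to cases where taking part becomes unsafe or impractical.
- **The losses overlap.** A reader might add all these removals to the planned 10% and 20% and conclude that 210 cannot be reached. Missed follow-up and deaths are already in those allowances; only eliminations under 2.3.4 are clearly extra, and their number is unknown.
- **The direction is not given.** A reader might infer that results will look too favourable. That is plausible for deterioration. For treated children it depends on who is treated and with what effect, which the document does not state.
- **The reach is unknown.** Since entry requires encephalopathy or seizures, a reader might suppose that most of the cohort would be eliminated. The article names no confounding treatments, and a list may stand in the full protocol.
- **The authors see part of the problem.** The Discussion acknowledges attrition related to severity or socioeconomic factors, and 2.4.2 provides for follow-up at any centre, cost support and gifts.
- **The unsafe-or-impractical criterion protects participants** and should not be struck out on statistical grounds.

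None of this answers the elimination rule. Even a precise list of confounding treatments would still remove children for treatment received, against the study's own objectives.

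**Conclusion.** The concern holds for 2.3.4, and in a weaker form for 2.3.3. The treatment and deviation elimination criteria contradict the secondary objectives, the therapy module and the promise to adjust for changes in practice. If followed, they select the analysis set after enrolment. That conclusion comes from the text alone and needs no assumption.

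The size does rest on assumptions. Under the shares shown, the effect runs from no shift in the 30% rate with about 57 events to a rate of 19.2% with about 32 events. With 10% removed equally, events per variable fall below 10 even with 6 predictors. The document does not support a firm direction for treated children, a claim that most of the cohort would go, or a claim that withdrawals push the sample below 210.

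For 2.3.3, the defect is that the effect of withdrawal on the analysis set is unstated, while its triggers can cost observable 5-year outcomes and are partly related to prognosis. The point should be settled before children are dropped, because a 5-year outcome missed through early withdrawal is hard to recover.

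**What to change.** - In 2.3.4, delete the treatment and protocol-deviation elimination criteria. Analyse every enrolled, centrally confirmed case.
- Record treatments as descriptors or covariates, according to the analysis.
- Treat a missed visit as missing data for that visit, with the child still due at 5 years.
- State that children withdrawn for any reason stay in the analysis set, including the incidence count, with data collected to that point and, where consent allows, survival and outcome status from records.
- Keep the safety-related withdrawal criterion, but reconcile it with the survival and 5-year outcomes so that leaving active follow-up does not mean leaving the analysis. What counts as unsafe is for the investigators.

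The cost is protocol wording and a little more analysis and follow-up work, since some children who would have been withdrawn remain due for later visits. No additional enrolment is needed.
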